#### Neuropsychological assessments

2.5.3

Neuropsychological evaluations will assess six principal cognitive domains:

Memory.Temporal and spatial orientation.Executive function.Visuospatial ability.Attention and calculation.Language.

These domains will be evaluated using standardized instruments, including:

Mini-Mental State Examination (MMSE).Montreal Cognitive Assessment (MoCA).Rey Auditory Verbal Learning Test.Stroop Color and Word Test.Digit Span Test (Nasiri et al., 2023).Boston Naming Test - Short Form (total score = 15).

#### Plasma and fecal metabolome analysis by LC–MS/MS

2.5.4

For fecal metabolite extraction, stool samples were homogenized with 3 mL of ethanol, followed by centrifugation, and 100 μL of the resulting supernatant was collected and vacuum-dried. For plasma samples, protein precipitation was performed by adding methanol to a 20 μL aliquot at a 1:4 (v/v) ratio; the supernatant was collected and vacuum-dried. Both dried extracts were reconstituted in 20 μL of 5% (v/v) aqueous methanol containing 250 fmol isotopically labeled internal standards, of which 5 μL was injected for LC–MS/MS analysis. Chromatographic separation was performed on an Atlantis T3 column (3 μm, 100 Å, 2.1 × 150 mm, Waters) at 35 °C and 250 μL/min, using 0.1% formic acid in water (mobile phase A) and acetonitrile (mobile phase B), with a gradient of 1% B for 1 min, ramping to 40% B over 14 min, 80% B over 3 min, held for 3 min, and re-equilibrated at 1% B for 5 min (total run time: 25 min). Mass spectrometric detection was performed on a QTRAP 6500 + system (AB Sciex) in both negative and positive ion modes; in negative mode, CUR, CAD, and IS were set at 25 psi, 12, and −4,500 V, respectively, and in positive mode at 25 psi, 10, and +5,500 V, with source temperature, GS1, and GS2 maintained at 500 °C, 50 psi, and 60 psi for both modes. Targeted quantification was conducted in MRM mode, with precursor ion, product ion, and retention time individually predefined for each analyte; peak areas were integrated using Analyst software (AB Sciex).

#### Gut microbiota profiling by full-length 16S rRNA gene sequencing

2.5.5

Full-length 16S rRNA gene sequencing will be performed using the PacBio Revio platform, enabling species-level taxonomic resolution for precise identification of microbial strains capable of producing neuroactive metabolites. PCR amplification will be conducted using universal primers 27F and 1492R, followed by SMRTbell library preparation and sequencing, yielding approximately 10,000 high-quality circular consensus sequencing (CCS) reads (Q30) per sample. Bioinformatic processing will be performed using QIIME2, with taxonomic classification based on the SILVA database. Downstream analyses will include alpha and beta diversity indices (e.g., Shannon index), taxonomic annotation, and differential abundance analysis between study groups using DESeq2. DNA extraction and library preparation procedures will follow those described by Tsai et al. (2025).

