### Aims, study design, and settings

2.1

This study aims to estimate preliminary effect sizes to inform sample sizes for future definitive trials, evaluate the feasibility and acceptability of memorization practice and multimodal assessments, and generate mechanistic hypotheses about the relationship among recitation practice, neuroimaging biomarkers, and gut-brain axis markers, particularly for individuals with SCD. By analyzing changes in fMRI, neuropsychological assessments, and physiological biomarkers, including blood sampling, plasma metabolomic profiling, and fecal microbiota and metabolomic analyses, we seek to elucidate both the short-term practicability of structured recitation training and its underlying neurobiological mechanisms in SCD. Regarding long-term implications, our database will primarily consist of Chinese-speaking Asian participants. The longitudinal follow-up data will enable a more comprehensive understanding of the progression of SCD within this specific population, thereby addressing an underrepresented demographic in current SCD research.

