Following completion of the initial six-month intervention phase, participants will be given the option to voluntarily continue recitation practice. The selection of a six-month intervention period is informed by the MEMO+ (Méthode d’Entrainement pour Mémoire Optimale) protocol developed by Sylvie Belleville and colleagues (Bier et al., 2015). Later studies from the same research team have demonstrated that participants receiving structured cognitive training exhibited significant improvements in memory recall performance, with effects persisting for at least 6 months post-intervention (Belleville et al., 2018). Furthermore, long-term follow-up over 5 years revealed that individuals who had undergone cognitive training experienced a slower decline in delayed memory performance and Montreal Cognitive Assessment (MoCA) scores compared with control groups (Belleville et al., 2024). These findings underscore the sustained benefits and potential long-term impact of continuous cognitive training.

Additional support for the selected intervention duration is derived from studies examining other forms of cognitively engaging activities. For example, interventions involving structured calligraphy practice have demonstrated that extending training duration over a six-month period leads to significant alterations in functional brain connectivity (Lee et al., 2024). Specifically, increased connectivity has been observed between the medial prefrontal cortex (mPFC) and right lateral temporal cortex (LTC), mPFC and right inferior parietal lobe (IPL), left hippocampal formation (HF) and right LTC, as well as between the left HF and right IPL (Lee et al., 2024). These findings suggest that prolonged engagement (6 months) in cognitively demanding tasks may induce measurable neuro-modulatory effects at the network level.

Taken together, a 6-month intervention period represents a balanced design choice: it is sufficiently long to allow for detectable behavioral and neurobiological changes, yet not so prolonged as to compromise participant adherence. Accordingly, outcome assessments will be conducted at baseline (time of recruitment), immediately after the six-month intervention, and at one-year and two-year follow-ups, with annual assessments thereafter until participants are no longer able to complete evaluations. The study will be conducted at China Medical University Hospital, primarily within the outpatient clinics of the Departments of Neurology or Psychiatry.

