##### Statistical analysis

2.5.2.5

Statistical analyses will be conducted within the framework of the general linear model (GLM). For the primary clinical outcomes (e.g., subjective cognitive measures, neuropsychological test scores), a linear mixed-effects model will be used to handle the repeated-measures structure of the data throughout baseline, post-intervention, and follow-ups, with time, group, and group × time interaction as fixed effects, and subject as a random effect. This approach naturally accommodates missing data under the missing-at-random (MAR) assumption without requiring complete cases. The primary analysis will follow the intention-to-treat principle, including all randomized participants regardless of adherence or dropout, with missing values handled using multiple imputation based on baseline characteristics and available follow-up data. A per-protocol sensitivity analysis will also be conducted, restricted to participants who complete at least 80% of the intervention sessions. Covariates to be included in adjusted models will comprise age, sex, years of education, and baseline cognitive scores, selected *a priori* for their known associations with cognitive outcomes in SCD populations.

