### Statistical methods

2.6

The primary efficacy analysis will be conducted using generalized linear mixed-effects models to analyze repeated measures data, with adjustment for relevant covariates. Microbiome analyses will be performed using DESeq2 to identify differentially abundant taxa and linear discriminant analysis effect size to detect potential microbial biomarkers. Metabolomic data will be analyzed using partial least squares discriminant analysis, and pathway enrichment analysis will be conducted using the MetaboAnalyst platform. Multi-omics integration will be performed using Spearman correlation-based network analysis and causal mediation analysis to investigate regulatory mechanisms along the gut-brain axis. Multiple comparisons will be corrected using FDR, with a threshold of *q* < 0.05. All statistical analyses will be conducted using R (version 4.4.0; R Core Team, 2024) and SPSS (version 29.0; IBM Corp., Armonk, NY, USA), with statistical significance set at *p* < 0.05.

Given the inherent complexity and multi-layered nature of multi-omics data, if the aforementioned methods are insufficient for comprehensive analysis, we will collaborate with the institutional Artificial Intelligence Center affiliated in our hospital to implement advanced analytical approaches. These may include machine learning, network-based modeling, and partial least squares regression, among others, to construct predictive models that characterize causal or associative relationships between biological markers and clinical outcomes (e.g., cognitive function and depression). The predictive performance of different models will be systematically compared.

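### The microbiome and metabolome aims concern change, but the analyses named for them contain no baseline, participant or group-by-time term

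*Protocol article*

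**What the plan says.** **Target.** Section 2.1 sets out the aim as follows: "By analyzing changes in fMRI, neuropsychological assessments, and physiological biomarkers, including blood sampling, plasma metabolomic profiling, and fecal microbiota and metabolomic analyses". Section 3.1 hypothesises shifts in microbiota composition and in circulating metabolites. Section 3.3 expects diversity and certain genera to rise relative to controls.

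**Timing.** Section 2.1 also says that "outcome assessments will be conducted at baseline (time of recruitment), immediately after the six-month intervention, and at one-year and two-year follow-ups", then annually. No outcome is exempted, and section 2.5 lists microbiota diversity, microbiota composition and fecal metabolomics among the outcomes. The article gives no separate stool or plasma schedule.

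**Named omics methods.** Section 2.5.5 specifies "differential abundance analysis between study groups using DESeq2". Section 2.6 says "Microbiome analyses will be performed using DESeq2 to identify differentially abundant taxa and linear discriminant analysis effect size to detect potential microbial biomarkers" and "Metabolomic data will be analyzed using partial least squares discriminant analysis". The FDR threshold is q < 0.05.

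**Repeated-measures methods.** Section 2.5.2.5 says "For the primary clinical outcomes (e.g., subjective cognitive measures, neuropsychological test scores), a linear mixed-effects model will be used", with group, time, their interaction and a subject random effect. Section 2.6 says "The primary efficacy analysis will be conducted using generalized linear mixed-effects models to analyze repeated measures data".

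**Status.** Section 3.3 calls the microbiota and metabolomic measures exploratory and reports them descriptively, with effect sizes and 95% intervals. Section 2.5 lists microbiota and fecal metabolomics as secondary.

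**The concern.** A question about change in a randomised trial is best answered by comparing arms at six months given each person's starting value. Gut and metabolite profiles may differ between people for reasons unrelated to the training, and a baseline sample can remove part of that variation. The tools named for the omics data work on group labels. In standard form, LEfSe and PLS-DA estimate neither a baseline-adjusted difference nor a group-by-time effect, and they do not allow for two samples coming from one person.

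The authors do spell out repeated-measures modelling, but they attach it to the clinical outcomes and the primary efficacy analysis. The text therefore names a method for the omics data that fits the stated aim poorly, which is more than leaving a detail open.

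At stake is the precision of the effect estimates and candidate-marker lists that these outcomes are meant to hand to a later trial. A second risk is that an analyst facing several samples per person and a two-group tool enters them all as separate samples.

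**Working it through.** **The plan's own figure.** The article gives no precision or power figure for the omics outcomes. Its only power calculation (section 2.3: d = 0.18, one-sided 0.05, 80% power) reproduces exactly by the noncentral t: 383 per group, power 0.8006. It concerns neuropsychological scores and plays no part below.

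**Inputs**
- 30 per arm (section 2.3).
- Baseline-to-six-month correlation r of one feature: not in the document. Assumed to be 0.3, 0.5 or 0.7.
- One feature on a roughly normal scale, such as the Shannon index, with SD 1 at each visit; two-sided 5% test, 80% power, no FDR penalty.

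**Step 1: precision.** Relative to a six-month-only comparison (variance 1), the variance is 1 − r² with the baseline value as covariate and 2(1 − r) for a change score. The detectable difference is (1.960 + 0.842) × √(2/30 × variance factor). The equivalent unadjusted size is 30/(1 − r²).

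| r | 1 − r² | Variance forgone | Detectable, six-month only | Detectable, baseline-adjusted | 30 adjusted is worth |
|---|---|---|---|---|---|
| 0.3 | 0.91 | 9% | 0.72 SD | 0.69 SD | 33 per arm |
| 0.5 | 0.75 | 25% | 0.72 SD | 0.63 SD | 40 per arm |
| 0.7 | 0.51 | 51% | 0.72 SD | 0.52 SD | 59 per arm |

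A stricter per-feature threshold raises every detectable difference. The ratio of adjusted to unadjusted, √(1 − r²) = 0.95, 0.87 and 0.71, does not depend on the threshold in this approximation.

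**Step 2: change scores.** The factor 2(1 − r) is 1.40, 1.00 and 0.60, giving detectable differences of 0.86, 0.72 and 0.56 SD. At r = 0.3 this is worse than ignoring baseline, so the form of adjustment matters.

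**Step 3: pooling, as a hazard to exclude.** If both visits enter as independent samples, the true variance of an arm mean is (1 + r) times the variance the test assumes. The nominal 5% test then rejects under the null with probability 2[1 − Φ(1.96/√(1 + r))]:
- r = 0.3: 1.96/√1.3 = 1.72, giving 8.6%
- r = 0.5: 1.96/√1.5 = 1.60, giving 11.0%
- r = 0.7: 1.96/√1.7 = 1.50, giving 13.3%

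Simulated t-tests (30 per arm, 20,000 null trials per setting) gave 8.7%, 11.4% and 13.9%, and rank-sum tests (4,000 trials) gave 9.0%, 10.7% and 13.5%. The range is therefore about 9-14%.

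**The case against.** The strongest reply is that the article only names tools. It gives no visit and no design formula, and a randomised comparison of change is also a comparison between study groups. DESeq2 fits a user-specified design that can carry baseline, visit, interaction and fixed participant terms. The article is condensed, an analysis plan may supply the model, and the outcomes are exploratory.

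Much of this stands, and it rules out two stronger readings that a reader might infer.
- **That the protocol states a cross-sectional test.** No section says so. The visit compared is left open, and the DESeq2 wording alone does not exclude a baseline-aware design.
- **That the protocol pools visits and will therefore report false taxa and metabolites.** No section proposes pooling. The other simple reading, six-month samples only, is unbiased under randomisation and costs precision alone.

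Two limits on the figures also stand. The correlation is assumed, and at 0.3 the gain is small. The detectable differences are for a single feature before FDR control and do not carry over directly to sparse sequence counts. Baseline stool and plasma sampling is itself inferred from the general visit schedule and the stated interest in change.

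What the reply does not remove is the mismatch for LEfSe and PLS-DA. A later document can add a design formula to DESeq2, but the other two in standard form do not answer a question about change. Nor does it explain why repeated-measures models are named for other outcomes and not for these.

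**Conclusion.** The point holds as a mismatch between aim and named method. The omics questions are about change and baseline assessments are scheduled, yet the methods named for them carry no baseline, participant or group-by-time term.

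If the analysis became a six-month-only comparison, the loss would be one of precision: 9% to 51% of residual variance for r from 0.3 to 0.7. Pooling would be an error of validity, but it is a possibility to close off and not something the protocol commits to.

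The sizes rest on the assumed correlation, equal variances at the two visits and a normally scaled feature. Severity is minor to moderate: the outcomes are exploratory and the primary result is untouched, but these estimates are intended to inform the next trial.

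**What to change.** In sections 2.5.5 and 2.6, state that:
- the between-group comparison of each taxon, each metabolite and the Shannon index is made at six months and adjusts for the participant's own baseline value;
- a model with group-by-time and a participant term is an acceptable alternative. With two visits and unconstrained baseline means it estimates the difference in change, so the covariate form is preferable where the correlation may be low;
- FDR control at q < 0.05 across features is kept;
- DESeq2 may stay, provided that its design includes baseline or visit and participant terms;
- LEfSe and PLS-DA are descriptive displays, each using one sample per participant from a named visit;
- samples from different visits are never entered as independent observations.

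It would also help to confirm the stool and plasma sampling visits and to give these outcomes one status, since section 2.5 and section 3.3 differ. The cost is wording and modest extra analysis work. No samples are needed beyond those the visit schedule already implies.

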### Statistical methods

2.6

The primary efficacy analysis will be conducted using generalized linear mixed-effects models to analyze repeated measures data, with adjustment for relevant covariates. Microbiome analyses will be performed using DESeq2 to identify differentially abundant taxa and linear discriminant analysis effect size to detect potential microbial biomarkers. Metabolomic data will be analyzed using partial least squares discriminant analysis, and pathway enrichment analysis will be conducted using the MetaboAnalyst platform. Multi-omics integration will be performed using Spearman correlation-based network analysis and causal mediation analysis to investigate regulatory mechanisms along the gut-brain axis. Multiple comparisons will be corrected using FDR, with a threshold of *q* < 0.05. All statistical analyses will be conducted using R (version 4.4.0; R Core Team, 2024) and SPSS (version 29.0; IBM Corp., Armonk, NY, USA), with statistical significance set at *p* < 0.05.

Given the inherent complexity and multi-layered nature of multi-omics data, if the aforementioned methods are insufficient for comprehensive analysis, we will collaborate with the institutional Artificial Intelligence Center affiliated in our hospital to implement advanced analytical approaches. These may include machine learning, network-based modeling, and partial least squares regression, among others, to construct predictive models that characterize causal or associative relationships between biological markers and clinical outcomes (e.g., cognitive function and depression). The predictive performance of different models will be systematically compared.

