### Sample size

2.3

Our sample size calculation is based on selecting functional MRI changes as an exploratory mechanistic outcome measure, given their higher sensitivity than neuropsychological tests at the preclinical stage in SCD patients (Viviano and Damoiseaux, 2020). This approach differs from many previous cognitive intervention studies that have used neuropsychological test scores as primary outcomes. The target sample size is informed by prior neuroimaging studies in individuals with SCD, where changes in functional MRI parameters served as the primary outcomes (Bhome et al., 2018), while also considering feasibility constraints (Belleville et al., 2023). Accordingly, we plan to recruit 60 participants, with 30 individuals allocated to each group. To account for an anticipated attrition rate of approximately 20%, based on dropout rates reported in comparable longitudinal cognitive intervention studies in older adults (Cheng et al., 2024; Fernandez-Gamez et al., 2026), we will initially enroll 72 participants (36 per group), with the expectation that at least 60 will complete the study.

If neuropsychological test scores were used as the primary outcome, a substantially larger sample size would be required. An *a priori* power analysis was conducted using G*Power version 3.1.9.4 (Heinrich Heine University, Düsseldorf, Germany), based on a two-group comparison of continuous outcomes within the t-test family (“Means: Difference between two independent means”). Equal group allocation was assumed (N₂/N₁ = 1), and a one-tailed test was selected given the directional hypothesis that the intervention would improve outcomes. The anticipated standardized effect size was set at Cohen’s d = 0.18, derived from prior meta-analytic evidence indicating a small-to-moderate effect consistent with neuroimaging-based outcomes in SCD populations (Bhome et al., 2018). With a Type I error rate (*α*) of 0.05 and statistical power (1 − *β*) of 0.80, the estimated required sample size would be 383 participants per group (total *N* = 766; df = 764; actual power = 0.8006). Given the extensive multimodal assessments and longitudinal design of the present study, recruiting a sample of this magnitude is not feasible. Therefore, this study is designed as an exploratory, hypothesis-generating trial with a smaller sample size, aiming to provide preliminary effect estimates and inform future large-scale confirmatory studies.

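### PLS-DA is the only between-group analysis named for the metabolome, yet it supplies neither the error control of section 2.6 nor the interval estimates promised in section 3.3

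*Protocol article*

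**What the plan says.** All statements are in the protocol article.

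- **Metabolomic method (2.6).** "Metabolomic data will be analyzed using partial least squares discriminant analysis", with pathway enrichment afterwards. The sentence does not name the classes. Arm is the natural reading, because section 3.1 hypothesises that recitation is associated with shifts in metabolomic profiles.
- **Contrast with the microbiome (2.5.5, 2.6).** Taxa are tested one by one between study groups with DESeq2. No per-analyte counterpart is named for metabolites.
- **Error control (2.6).** FDR with q < 0.05 for multiple comparisons, and p < 0.05 for significance.
- **Fallback (2.6).** "if the aforementioned methods are insufficient for comprehensive analysis", machine learning and related methods may be used "to construct predictive models that characterize causal or associative relationships between biological markers and clinical outcomes", with cognitive function and depression as examples of the outcomes. Then: "The predictive performance of different models will be systematically compared".
- **Panel (2.5.4).** Targeted quantification "with precursor ion, product ion, and retention time individually predefined for each analyte". The number of analytes is not given.
- **Status.** Section 2.5 lists fecal metabolomic profiles among the secondary outcomes. Section 3.3 makes metabolomic measures exploratory, meant to yield effect-size estimates and candidate biomarkers. It promises descriptive reporting with effect sizes and 95% confidence intervals.
- **Numbers (2.3).** "we plan to recruit 60 participants, with 30 individuals allocated to each group", and "we will initially enroll 72 participants (36 per group), with the expectation that at least 60 will complete the study", at about 20% attrition.

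**The concern.** There are two separate problems.

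First, the named method does not produce what the document says will be controlled and reported. PLS-DA chooses weights that maximise covariance between the analytes and the class label. With analytes as numerous as participants, or more so, it finds a separating direction whether or not one exists in the population. The FDR rule cannot protect against this because PLS-DA produces no set of p-values for it to act on. A loading or importance score is also not a between-arm effect with a confidence interval.

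Second, the fallback sentence claims too much. Its models relate markers to clinical outcomes, and neither of these is randomised, so good prediction does not identify a cause. If performance were judged on the data used for fitting, it would also be optimistic.

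At stake is the pilot's list of candidate metabolites for the next trial. False candidates are the costly error there. Section 3.1 itself faults this literature for biases that inflate apparent effects.

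**Working it through.** **Figures in the plan.** The document gives no figure for PLS-DA or model performance, so none can be reproduced. The only relevant figure is the number analysed. The document's 72 equals 60 × 1.2. At 20% attrition, 72 × 0.80 = 57.6, so about 57 remain rather than 60. That mismatch is a separate matter; both 57 and 60 were tried here.

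**Inputs.** N = 57 or 60 in two near-equal arms (section 2.3). Number of analytes p = 20 to 500, and their correlation, are assumptions. There is no true arm difference.

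**Hand check with one component.** Take p independent standardised analytes.
1. Under the null, each observed mean difference between arms has variance of about 4/N.
2. The first PLS weight vector points along the vector of observed differences, so the arms' mean scores differ by about √(4p/N) within-arm standard deviations.
3. Apparent accuracy ≈ Φ(½√(4p/N)).

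With N = 57:

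| p | √(4p/57) | apparent accuracy |
|---|---|---|
| 20 | 1.18 | 72% |
| 50 | 1.87 | 83% |
| 100 | 2.65 | 91% |
| 200 | 3.75 | 97% |
| 500 | 5.92 | 99.8% |

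With N = 60 and p = 100, √(400/60) = 2.58, giving 90%.

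**Simulation with two components.** NIPALS PLS on autoscaled data, arm coded 0/1, predicted arm = 1 if the fitted value exceeds 0.5; 200 null datasets per cell, N = 57. Analytes are independent, or in blocks of 10 with correlation 0.5. Cross-validation is 7-fold, and Q² = 1 − Σ(y − ŷ_cv)² / Σ(y − ȳ)².

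| p | in-sample, independent | in-sample, correlated | cross-validated (independent / correlated) |
|---|---|---|---|
| 20 | 76% | 73% | 50% / 48% |
| 50 | 91% | 83% | 49% / 49% |
| 100 | 99% | 91% | 48% / 49% |
| 200 | 100% | 98% | 49% / 49% |
| 500 | 100% | 100% | 48% / 49% |

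Mean Q² is negative in every cell, from −0.15 to −1.03 across two and three components. A third component raises in-sample accuracy further (for example from 91% to 97% at p = 100, correlated).

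**Other settings.** A separate simulation with a 10-factor correlation structure, 29 versus 28 people and 150 datasets gave 94%, 98% and 99.7% in-sample at p = 100, 200 and 500, with 48-49% under 5-fold cross-validation. Moving from N = 57 to N = 60 (300 datasets, independent analytes) changes in-sample accuracy from 75.3% to 75.5% at p = 20 and from 98.7% to 98.4% at p = 100, which is immaterial.

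**Fallback comparison.** If several models of a two-class outcome all performed at chance on 57 people and the best were singled out, its mean accuracy would be about 55-56% for 3 models, 56-58% for 5 and 58-60% for 10, against 50% for one. The document does not say that a best model will be singled out, so this only bounds a possible effect.

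**The case against.** The strongest case against is that much of this rests on silence. Folds, permutations and component selection are details that a condensed article commonly leaves to a full protocol or analysis plan, and neither is shown. The document does not say that an in-sample score plot or accuracy will be the evidence. It labels these measures exploratory and not powered for confirmation, and it applies FDR in the same paragraph. The panel is targeted and may be small.

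Most of this stands. A reader might infer that no validation is planned and that the arms will look separated whatever happens; the text does not support that. Separation under the null is conditional on in-sample reporting, and its size depends on an unstated analyte count.

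A reader might also infer that the machine-learning step adds to spurious arm separation, or that a winning model will be picked for its optimism. The text supports neither. The step is conditional, its models predict clinical outcomes rather than arm, and it promises only a comparison, with no rule for choosing a winner.

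Three things do not depend on silence. The named group method yields no p-values for the stated FDR rule. It does not yield the promised effect sizes and intervals. And the predictive-model sentence claims causal content that prediction cannot supply. The exploratory label does not cure these, because identifying candidate biomarkers is the stated use.

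**Conclusion.** The concern holds in this limited form. PLS-DA, as the only named group analysis of the metabolome, does not deliver the error control or the estimates to which the article commits itself. Reported in-sample, it would show about 73-76% apparent accuracy under the null at 20 analytes, 83-91% at 50 and 91-100% at 100 to 500, against about 48-50% cross-validated. These figures assume two components, Gaussian analytes, arm as the class and the analyte counts shown. The qualitative result does not depend on 57 versus 60 participants or on the correlation structures tried.

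For the fallback, the wording on causation is wrong as it stands. Optimistic performance is a risk only if it is judged on the data used for fitting. The change is worth making, but the primary conclusion of the trial is not affected.

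**What to change.** 1. In section 2.6, make the main metabolomic comparison a between-arm model for each analyte, adjusted for its baseline level where measured, reporting effect size, 95% CI and an FDR-adjusted value. This gives the q < 0.05 rule something to act on and meets the reporting promise in section 3.3.
2. State that PLS-DA and any fallback model are reported only as cross-validated performance, nested where components or models are tuned.
3. For PLS-DA, add a permutation p-value that re-randomises arm within the age and sex strata used for allocation.
4. Remove the word causal from the predictive-model sentence and keep the associative wording. The separately planned causal mediation analysis is not touched by this edit.

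The cost is a few sentences and a little computing time, with no change to participants, visits or assays. The downside is that some visually striking plots will be reported as null.
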